### Evaluation Frameworks and Outcomes

#### Quantitative Evaluation

We will leverage the RE-AIM (reach, effectiveness, adoption, implementation, and maintenance) framework (Table 3) to quantitatively evaluate feasibility, reach, effectiveness, and intervention implementation.

Per our first study objective, we aim to evaluate the feasibility of implementing this intervention in the safety-net, ambulatory HIV care setting, which we will assess using various domains of the RE-AIM evaluation framework. Our primary outcome will be defined via engagement: 50% CM visit attendance will indicate a threshold for program feasibility. Secondary feasibility outcomes will include number of visits performed, average visit time, and monetary value earned per participant, which map to domains (Table 3). Metrics related to “reach” will assess if the proposed implementation model will be used by a diverse patient population with complex sociomedical needs (as intended), reflecting both the utility and accessibility of this program. “Effectiveness” metrics will seek to establish if the intervention modified the target behavior changes, leading to reduced stimulant use, improved ART adherence, and undetectable HIV viral loads. “Implementation” metrics will describe the costs required to start and maintain this program during the study period (8 months). Our secondary outcome is preliminary effectiveness, which we will determine using proportion of stimulant-negative and tenofovir-positive urine tests, as well as changes in HIV viral suppression before and after participation. We will report missing data and impute missing viral load data as >200 copies/mL.

**Table 3 table3:** RE-AIM (reach, effectiveness, adoption, implementation, and maintenance) framework evaluation of dual-incentive contingency management targeting antiretroviral therapy adherence and stimulant use in ambulatory HIV care.

Dimension	Question	Outcomes
Reach	Will safety-net patients living with HIV and stimulant use disorder enroll in this program? Will they return after enrollment?	Sociodemographics Substance use and HIV histories Proportion of study visits attended
Effectiveness	Will participants reduce stimulant use? Will participants improve tenofovir adherence?	Weekly point-of-care results and 7-d timeline follow-back
Adoption	Will offering this program in the ambulatory HIV care setting be acceptable to staff and participants? What changes, if any, would make the program more or less acceptable?	Qualitative evaluation
Implementation	What were the monetary and other resource costs of program implementation?	Length of visits Total gift cards provided (amount in US $) Proportion of incentives earned for stimulant use versus tenofovir adherence Number of point-of-care tests used Time spent on participant outreach
Maintenance	Not assessed in this pilot	—^a^

^a^Not applicable.

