Leveraging harm reduction principles will be essential for addressing the needs of safety-net populations with comorbid HIV and stimulant use disorder. Abstinence from stimulants can be an unrealistic, unwanted, or a less proximate goal for people with severe stimulant use disorder, who may be using daily or chronically [22]. Efforts to emphasize stimulant use reduction rather than abstinence have shown promise in promoting overall health; for example, in a secondary analysis of 13 randomized controlled trials, reduced use of methamphetamine and cocaine was associated with global improvement of psychosocial functioning and severity of drug-related problems, as well as improved depression and fewer drug-seeking behaviors [23]. Although CM is traditionally structured to promote abstinence, new models that incentivize stimulant use reduction and other positive health behaviors may be more aligned with patient goals and needs in the safety-net setting.

To optimize care for safety-net populations living with comorbid stimulant use disorder and HIV, we designed a novel CM program incentivizing both stimulant use reduction and ART adherence in the HIV ambulatory setting, called CoMBo (Contingency Management for Both HIV and Stimulant Use Disorder). CoMBo involves point-of-care (POC) tests that detect stimulant use within a 3- to 4-day window and offer once-weekly visits in contrast to traditional CM programs that test urine 2 to 3 times per week to confirm abstinence. In addition, we use a novel POC, a urine-based tenofovir assay that allows for real-time assessment of adherence to tenofovir-based ART [24,25]. This technology enables simultaneous assessment of tenofovir adherence and stimulant use by using one urine sample, facilitating a truly paired intervention.

In this paper, we present a full description of an implementation effectiveness pilot delivering CM with paired incentives in the HIV ambulatory setting and describe a protocol for the quantitative and qualitative evaluation of program feasibility and acceptability (the CoMBo study). We hypothesize that (1) this program will be acceptable to staff and participants and (2) offering once-weekly CM (as opposed to multiple-times per week) to achieve stimulant reduction (as opposed to abstinence) in low-barrier medical homes of people living with HIV will be feasible.

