## Methods

### CoMBo Study Design

We will conduct a pilot, single-arm, hybrid implementation effectiveness trial of dual-incentive CM targeting stimulant use reduction and improved ART adherence in 2 low-barrier, ambulatory HIV clinics. We use the Behavior Change Wheel framework to tailor this intervention to meet the needs of our target safety-net population (Table 1). This study design will allow for the investigation of implementation feasibility in our target setting, while also gathering data on the intervention’s impact on target behaviors. The study will occur over a period of 9 months; patient recruitment will occur during the first 6 months of the study on a rolling basis. Following this pilot, we will solicit feedback on intervention acceptability using in-depth qualitative interviews with participants and clinic staff. The study has been registered as a clinical trial (ClinicalTrials.gov NCT06564792).

**Table 1 table1:** Formative intervention components for targeting behavior change in safety-net ambulatory care, as described by the Behavior Change Wheel framework [26].

Source of behavior	Example of barriers to behavior change	Intervention component	How will intervention component facilitate behavior change?
Motivation (reflective and automatic)	Complete abstinence following a long period of dependence may be unrealistic, intimidating, or unwanted	1. Assess stimulant use reduction using once weekly using point-of-care tests with a 2- to 4-day detection window	Incentivization: create expectation of reward
Motivation (reflective)	Internalized stigma around psychosocial factors (eg, substance use and housing instability) leads to low self-belief in ability to change behavior	2. Engage in motivational interviewing, emphasizing self-talk and goal setting and providing social support	Persuasion: induce positive or negative feelings to stimulate actions
Opportunity (physical and social)	Limited resources to schedule and keep consistent in-person appointments (eg, limited access to phone, transportation)	3. Offer drop-in, one-on-one visits	Environmental restructuring: change physical and social context

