#### Incentivizing Stimulant Use Reduction

We hypothesize that incentivizing stimulant use reduction rather than abstinence will be acceptable to our target safety-net population with comorbid stimulant use disorder and HIV. One challenge to incentivizing stimulant use reduction is that no POC tests measure quantitative levels of cocaine or methamphetamine and thus cannot determine if one positive result represents a reduction or increase in use compared to another positive result. To overcome this challenge, we will assess stimulant use once weekly using POC tests with an approximate 4-day detection window. This would theoretically allow participants to continue using substances some days of the week, but still test negative for stimulants on POC tests if they do not use in the days preceding testing. Given that (per inclusion criteria), participants endorse using stimulants most days of the week (if not daily), we theorize that a negative result will constitute a true sign of use reduction.

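### The sentence defining stimulant effectiveness names only the urine proportion, which records recent non-use; timeline follow-back should stand beside it and be analysed over all attended visits

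*Protocol article*

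**What the plan says.** All references are to the protocol article.

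- **Outcome definition.** Under Evaluation Frameworks and Outcomes (Quantitative Evaluation), the secondary outcome is preliminary effectiveness, "which we will determine using proportion of stimulant-negative and tenofovir-positive urine tests", plus change in HIV viral suppression. The Methods paragraph of the Abstract gives the same definition. Neither mentions frequency of use.
- **Table 3, Effectiveness row.** The question is "Will participants reduce stimulant use". The outcomes listed are "Weekly point-of-care results and 7-d timeline follow-back".
- **What the urine test can show.** The section Incentivizing Stimulant Use Reduction explains that the tests are not quantitative and "cannot determine if one positive result represents a reduction or increase in use compared to another positive result". Participants could go on using on some days and "still test negative for stimulants on POC tests if they do not use in the days preceding testing". Since entry requires near-daily use, the authors take a negative as a genuine sign of reduction.
- **Detection window.** That section says "we will assess stimulant use once weekly using POC tests with an approximate 4-day detection window". The Introduction (Background) describes "point-of-care (POC) tests that detect stimulant use within a 3- to 4-day window". Table 1 refers to "point-of-care tests with a 2- to 4-day detection window".
- **Frequency of use.** Assessment and Data Collection obtains a 7-day timeline follow-back at baseline and at each visit. The Analysis Plan reports average frequency from it and compares baseline with study visit 12 by a paired t test. Urine results are described only: proportions by week and overall, and the number of participants ever negative.

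**The concern.** The programme exists to credit reduction short of abstinence. The sentence that defines effectiveness nevertheless rests, for stimulants, on a yes/no measure that responds only when all use falls outside the detection window. The article argues in one direction, that a negative implies reduction. It does not say how to read a run of positives from someone who has cut down but still uses at some point in the days before the visit. In the urine proportion, that person looks the same as someone who has not changed.

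Two things are at stake. A low proportion of negatives could be read as little reduction when use has fallen substantially. The proportion also mixes how much people cut down with when in the week they stopped. The measure that could separate these is already collected, but it is missing from the defining sentence, and its only test uses one follow-up visit.

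**Working it through.** The article gives no power, sample-size or error figure for this outcome, so there is nothing to reproduce. The check asks how often a reduced level of use would produce a negative urine.

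**Inputs**
- Detection window w: 4 days (Incentivizing Stimulant Use Reduction), 3 to 4 days (Background), 2 to 4 days (Table 1). All of w = 2, 3 and 4 are tried.
- Visits: once weekly for 12 weeks (Intervention, Description).
- Starting level: the entry criterion is near-daily use, taken here as 7 days a week (assumption).
- Placement of use days: unknown. Two extremes are shown, random within the week and deliberately timed around the visit (assumptions).

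**Step 1: what needs no placement assumption.** A negative requires all k use days to fall in the 7 − w days outside the window. If k > 7 − w, a negative is impossible. For w = 4 this means k of 4 or more, so a fall from 7 to 4 days (3/7 = 43%) cannot show. For w = 3 the limit is 5 or more days, and for w = 2 it is 6 or more.

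**Step 2: random placement.** P(negative) = C(7 − w, k) / C(7, k).

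| Use days k | w = 4 | w = 3 | w = 2 |
|---|---|---|---|
| 1 | 42.9% | 57.1% | 71.4% |
| 2 | 14.3% | 28.6% | 47.6% |
| 3 | 2.9% | 11.4% | 28.6% |
| 4 | 0% | 2.9% | 14.3% |
| 5 | 0% | 0% | 4.8% |
| 6 or 7 | 0% | 0% | 0% |

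For example, at w = 4 and k = 3: C(3,3)/C(7,3) = 1/35 = 2.9%.

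**Step 3: over 12 visits, at k = 3 and w = 4** (a fall from 7 to 3 days, 4/7 = 57%).
- Random placement: 12 × 1/35 = 0.34 expected negatives. If visits are independent, the chance of never testing negative is (1 − 1/35)^12 = 0.71.
- All use timed outside the window: up to 12 of 12 negative.

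The same amount of use can therefore give almost no negatives or all negatives, depending only on timing.

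**Step 4: what the follow-back analysis covers.** Use days are recorded at baseline and at every visit. In the Analysis Plan, the visits before visit 12 feed only the reported averages; the paired test uses baseline and visit 12. A participant without visit 12 data has no pair and drops out. The document does not let one count how many that is. The feasibility threshold of 50% attendance shows that missed visits were expected, while the Results section says only that 37 patients were recruited and completed 12 weeks.

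**The case against.** A reader might infer that the trial scores any reduction short of about 4 use-free days as no effect. The document does not support this. Table 3 names timeline follow-back as an effectiveness outcome, and the Analysis Plan gives it the only hypothesis test on stimulant use. No section defines a positive urine as failure to reduce, and the urine results carry no success threshold or test. The Discussion also states as a limitation that reduction is assessed indirectly because no point-of-care test quantifies use.

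The random-placement figures can also be challenged, with reason. Participants are paid for negatives, attend on the same day each week and are given a visual guide to the incentives, so the design encourages them to keep the days before the visit free of use. For those who do so, the random figures are far too pessimistic. Under the 2- and 3-day windows, 4 use days a week can still yield a negative.

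Finally, this is a secondary, preliminary outcome in a single-arm pilot whose primary outcome is attendance. Urine negativity is the behaviour being rewarded, so reporting it is proper, and making self-report the outcome in its place would be a debatable trade.

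All of this stands, and it limits the point. It does not explain why the defining sentence and the Abstract omit a measure that Table 3 includes, or why the test of that measure rests on visit 12 alone. The disclosed limitation does not say in which direction the urine measure errs. The scope for timing supports the view that the proportion reflects scheduling as well as amount of use.

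**Conclusion.** The point holds in limited form. The definition of preliminary effectiveness is narrower than Table 3 and the Analysis Plan, and the one stimulant measure it names records recent non-use, not frequency.

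Under the 4-day window, use on 4 or more days a week can never give a negative; this follows from counting days and needs no assumption about placement. At 3 days a week the result runs from 2.9% per visit with random placement to 100% with timed use. The random-placement figures mark one end of a range and do not predict how participants will behave. The insensitivity is smaller under the 2- and 3-day windows, so its size cannot be settled until the three statements of the window agree.

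Smaller reductions are measured, by self-report, but the only planned test of them is confined to participants with visit 12 data. The primary feasibility outcome is unaffected.

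**What to change.** - **Abstract (Methods) and Evaluation Frameworks and Outcomes:** name change from baseline in timeline follow-back use days per 7 days as a stimulant effectiveness measure alongside the urine proportion, not in place of it.
- **Same places:** describe the urine proportion as no detectable use in the days just before the visit, and state that a positive urine is not evidence of no reduction.
- **Analysis Plan:** estimate the change in use days from all attended visits, for example with a repeated-measures model, instead of visit 12 alone. Weeks with no visit remain unobserved, so show the number of visits contributing.
- **Analysis Plan:** cross-tabulate each visit's urine result with change in use days from baseline, and report how many participants report fewer use days but never test negative.
- **Background, Table 1 and Incentivizing Stimulant Use Reduction:** reconcile the stated detection windows.

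The cost is some wording, one further estimate and one table, all from data already collected. There are two drawbacks. Use days are self-reported in an uncontrolled trial, which is why the urine result must stay beside them. The Results section says quantitative analysis had concluded by June 2025, so the added analyses should be labelled post hoc. The clearer outcome definition can also be carried into any larger trial that this pilot informs.

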#### Qualitative Evaluation

Per our second study objective, we will qualitatively evaluate program acceptability to participants and health care staff following the Consolidated Framework for Implementation Research (CFIR). Constructs describing acceptability are encompassed by “adoption” and seek to describe circumstances and factors that influence intervention engagement among participants and synergy within the ambulatory HIV care ecosystem.

### Sampling and Recruitment

Participants will be asked to engage in the qualitative evaluation following study completion (week 12 from enrollment), during either the end of their final study visit or when they return to the home clinic for routine care. Any participant who enrolled and completed at least one study visit will be eligible to enroll. Eligible staff will be identified by the study coordinator, who will recommend staff who meaningfully contributed feedback regarding the pilot rollout or who interfaced with the pilot’s day-to-day functioning. For example, we anticipate the clinic’s head nurses and primary social workers to meet this criteria.

### Data Collection

Interviews will occur at each home clinic during clinic hours. They will be conducted by 1 to 2 trained researchers with extensive experience conducting qualitative interviews and background in HIV or addiction medicine. Participants will be consented by the interviewer before the interview. In-depth interview guides have been developed using the CFIR framework in order to systematically evaluate setting, intervention, individual, and process characteristics influencing program acceptability (Table 4; Multimedia Appendices 2 and 3). All interviews will be recorded; the interviewer will refrain from using identifying language during the record process, for example, by using participants’ study ID numbers instead of their name. Interviews are estimated to last approximately 45 minutes. Each interviewee will receive US $50 worth of gift cards for their participation.

**Table 4 table4:** Consolidated Framework for Implementation Research (CFIR) framework for qualitative evaluation of program acceptability in low-barrier, ambulatory HIV care.

Target interviewees, CFIR domain, and CFIR construct				Question examples
**Care providers and staff who were involved with study participants (n=10)**				
	**Inner setting**			
		Compatibility	How compatible was this intervention with existing work processes at the clinic?	
		Tension for change	Is there a need for this intervention?	
		Relative priority	How important is it to provide this intervention, compared with other priorities?	
		Networks and communication	How have you referred participants?	
	**Characteristics of the individual**			
		Knowledge and beliefs	How do you feel about this intervention being offered at [clinic name]?	
**Participants who attended >50% of study visits (N=7); participants who attended <50% of study visits (N=7)**				
	**Intervention characteristics**			
		Relative advantage	How would your experience be different if you had to schedule visits instead of dropping-in?	
	**Process**			
		Engaging	How easy or difficult was it to participate in the program?	
		Executing	What did you think about getting urine results for both stimulants and tenofovir?	
		Reflecting and evaluation	How do you think you benefited from this program?	

### Participant Interviews

We will create a purposive sample of 14 trial participants, with priority recruitment of at least 7 participants who completed fewer than 50% of CM visits and 7 participants who completed more than 50% of CM visits (Table 4). This sample size will largely depend on the number of participants recruited, but we aim to interview approximately 30% of our total target sample size (ie, 14 participants in a pool of 40). Interviews will seek to (1) understand participant experiences in the primary care–based, stimulant, and adherence-targeted CM intervention and (2) explore how multilevel factors might positively and negatively influence engagement with multitarget CM (eg, role of relationships in the clinic, and concurrent synergistic clinical goals such as gender-affirming surgery, intervention factors such as drop-in visits, and reinforcement schedule, etc). We are secondarily interested in identifying how participant goals for stimulant use reduction are related to HIV management, if at all, and how drivers of stimulant use and additional determinants of health (eg, homelessness, intimate relationships, etc) interact with HIV and stimulant use disorder management.

### Care Provider and Staff Interviews

We will also conduct qualitative interviews with 5 to 10 care providers and staff who were involved in participants’ care or who interfaced with the intervention’s activities (eg, referred participants and assisted with program logistics). This final sample size will depend on how many care providers meaningfully interact with this pilot; we have identified a minimum of 5 care providers whose roles interface with the intervention, and we expect this number to increase as we integrate the problem into the everyday functioning of our target clinics. We seek to investigate perceived appropriateness of dual-incentive CM in the low-barrier HIV care context, elucidating perspectives on (1) the intervention’s compatibility with existing clinic processes, (2) how well the intervention met clinic needs and relative importance of these needs, and (3) changes to promote long-term sustainability.

### Analysis Plan

#### Quantitative Evaluation

We will analyze reach and implementation metrics (Table 3) using basic descriptive statistics. For effectiveness, we will use descriptive statistics to describe POC results, including the proportion of negative-stimulant and positive-tenofovir tests each week and cumulatively overall and the number of participants that test negative for stimulants or positive for tenofovir at least once. We will also report the average frequency of use as captured by weekly timeline follow-back and compare average use at baseline versus study visit 12 (ie, the final visit) using a paired 2-tailed *t* test. We will use the McNemar test to compare the proportion of participants with HIV viral loads less than 200 copies/mL before and after CM participation.

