### Intervention

#### Description

Enrolled participants who have provided informed consent will complete baseline surveys and urine testing (Table 2), then come to the clinic (in-person) once weekly for 12 weeks. During CM visits, participants will engage in motivational interviewing (MI) and provide urine for POC tenofovir and stimulant testing, with escalating incentives for a longer duration of stimulant-free and tenofovir-containing urine (Figure 1) [27]. Of note, incentives will not require both behavioral targets to be met. For example, if a participant’s urine tests positive for tenofovir but also for cocaine, they would receive draws for tenofovir but not for stimulants. At the next study visit, the stimulant-related draws would reset to 2 (if no stimulant in urine) with a rapid reset procedure for each target behavior following a lapse in target behavior (or missing sample).

**Table 2 table2:** Assessment variables and schedule for dual-incentive contingency management in HIV primary care.

Domain and assessment			Stage of collection		
			Baseline		Study visits

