### Assessment and Data Collection

All data will be captured and stored using REDCap electronic data capture tools hosted at University of California, San Francisco [35,36]. Most data metrics (described in Table 2) will be extracted from patient interviews during baseline and study visits, although viral loads will be extracted from patient’s electronic medical record.

Baseline assessments (Table 2) will extract patient variables relating to sociodemographics, substance use history, and HIV history, including HIV viral load before participation. We will also collect POC results at baseline (although no incentives will be earned from these results), perform 7-day timeline follow-back to assess baseline frequency of stimulant use, and record visit-related characteristics (length of visit and amount in US $ received through a priming draw; Multimedia Appendix 1) [37].

Visit assessments will assess recent stimulant use and ART adherence, capture POC results, and record visit characteristics (including number of incentives earned). At each visit, we will objectively assess each target behavior through POC testing (used to calculate incentives), subjectively assess stimulant use using 7-day timeline follow-back, and subjectively assess ART adherence using a 3-point Likert scale question (Table 2).

Upon intervention conclusion after 12 study visits, we will record the viral load most proximate to the patient’s last attended visit.

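### The urine analysis makes no use of the baseline urine result the trial collects, so it cannot by itself show change, chiefly for tenofovir adherence

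*Protocol article*

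**What the plan says.** Table 3 of the protocol article (Quantitative Evaluation, under Evaluation Frameworks and Outcomes) puts the effectiveness questions as "Will participants reduce stimulant use? Will participants improve tenofovir adherence". The outcomes listed beside them are the weekly point-of-care results and the 7-day timeline follow-back. The same section defines the secondary outcome as "proportion of stimulant-negative and tenofovir-positive urine tests, as well as changes in HIV viral suppression before and after participation". Viral suppression is thus framed as a change and the urine results as a level.

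The Analysis Plan describes the urine results by "the proportion of negative-stimulant and positive-tenofovir tests each week and cumulatively overall" and by "the number of participants that test negative for stimulants or positive for tenofovir at least once". It names baseline comparisons for two other measures. For self-reported use it will "compare average use at baseline versus study visit 12 (ie, the final visit) using a paired 2-tailed" t test, and for viral load it will use the "McNemar test to compare the proportion of participants with HIV viral loads less than 200 copies/mL before and after CM participation".

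A baseline urine result exists. Assessment and Data Collection states: "We will also collect POC results at baseline (although no incentives will be earned from these results". Table 2 lists tenofovir and stimulant detection at both baseline and study visits.

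**The concern.** Reducing and improving are changes from a starting point. A proportion of on-target tests during the program is a level. Without the starting level, a high and flat tenofovir-positive curve from week 1 could mean that the program raised adherence at once, or that participants were already taking their medication.

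The second reading is open because of the entry criteria. Suboptimal adherence is met by one viral load above 200 copies/mL, or a reported discontinuation, at any time in the preceding 18 months. A tenofovir-negative urine at entry is not required.

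The at-least-once count adds a second difficulty. It gives each participant up to 12 chances, so it grows with visits attended even if behavior does not change. It therefore mixes effectiveness with attendance, which is the primary feasibility outcome. The Discussion expects this pilot to inform larger trials, so a reader may take these urine figures as an early sign of effect.

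**Working it through.** **Which measures can show change.** From Table 2 and the Analysis Plan:

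| Measure | Baseline | Visits | Baseline comparison named |
|---|---|---|---|
| Urine tenofovir | yes | yes | no |
| Urine stimulants | yes | yes | no |
| 7-day timeline follow-back | yes | yes | yes, paired t test |
| 3-point Medication Adherence Assessment | yes | no | not possible |
| Weekly question (more, less or same as last week) | no | yes | not possible |
| Viral load below 200 copies/mL | before | after | yes, McNemar |

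Urine tenofovir is the only adherence measure taken at both times. Viral suppression lies downstream of adherence and measures it only indirectly.

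**The at-least-once count with no behavior change.** The article gives no per-test rate, so there is no figure of its own to reproduce. The number of tests comes from the Intervention description ("then come to the clinic (in-person) once weekly for 12 weeks"), so k = 12. I also take k = 6, which is 50% attendance. The per-test rate p and the within-person correlation are my assumptions.

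For independent tests, P(at least one) = 1 − (1 − p)^k:

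- p = 0.10: 1 − 0.90^12 = 72%; 1 − 0.90^6 = 47%.
- p = 0.30: 1 − 0.70^12 = 99%; 1 − 0.70^6 = 88%.

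Tests from one person are correlated, so a beta-binomial model is the sensitivity check. With correlation ρ, a = p(1 − ρ)/ρ and b = (1 − p)(1 − ρ)/ρ, P(at least one) = 1 − B(a, b + k)/B(a, b). At k = 12:

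| p | ρ = 0.2 | ρ = 0.5 | ρ = 0.8 |
|---|---|---|---|
| 0.10 | 46% | 27% | 16% |
| 0.30 | 86% | 64% | 43% |

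Every entry exceeds the per-test rate.

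**Stimulants.** Here the entry criterion of near-daily use constrains p. Assume u use days per week, independent days and a detection window of w days. Then p = (1 − u/7)^w. For example, u = 5 and w = 4 give (2/7)^4 = 0.0067, and 1 − (1 − 0.0067)^12 = 7.7%. The chance of at least one negative in 12 tests with unchanged use is:

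| Window | 5 use days | 6 use days |
|---|---|---|
| 4 days | 7.7% | 0.5% |
| 3 days | 25% | 3.4% |
| 2 days | 64% | 22% |

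The section on incentivizing stimulant use reduction gives an approximate 4-day window, the Introduction 3 to 4 days, and Table 1 2 to 4 days.

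**What restricting the count achieves.** Among those off target at baseline, the probability is 1 − P(none in 13)/P(none in 1). At ρ = 0.5 and k = 12, this is 20% at p = 0.10 (against 27%) and 49% at p = 0.30 (against 64%). Restriction removes those already on target and lowers the figure, but not to zero. With independent tests it would change nothing. The count therefore still needs the number of tests beside it.

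**The case against.** A reader might infer that the plan cannot show reduced use or improved adherence at all, and that the program will look successful whatever happens. The documents do not support that. Self-reported use has a paired comparison of baseline with visit 12, and timeline follow-back is one of the two effectiveness outcomes in Table 3. Viral suppression has a before/after test. No success threshold attaches to any urine summary; the only one is 50% visit attendance. The at-least-once count is one of three summaries, and the weekly proportions have no ceiling problem of this kind and would show a trend.

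The stimulant half is largely answered in the article, which argues that near-daily use at entry makes a negative result a sign of reduction. With a 4-day window the arithmetic agrees. The independent-tests figures of 72% to 99% are an upper case and do not carry over to stimulants.

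It can also be said that the list of summaries is introduced as non-exhaustive, and that a week-0 column may be left to a fuller document. That has some force. However, the same paragraph names baseline comparisons for two other measures and none for urine, and the secondary outcome is worded in the same way. The article also makes no argument for tenofovir like the one it makes for stimulants. Weekly proportions without week 0 still cannot separate an early gain from adherence already present. The point stands for tenofovir, and in weaker form for stimulants.

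**Conclusion.** The point holds in a limited form. The stated urine analysis omits a baseline comparison for which the data are collected, so the urine results by themselves cannot answer the Table 3 questions. For tenofovir no direct before/after analysis of adherence is stated anywhere. For stimulants the self-report comparison and the entry criterion cover much of the gap, unless the window is near the 2-day end of Table 1's range.

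The at-least-once count can be high with no change: over 12 tests, 72% to 99% under independence and about 27% to 64% at a within-person correlation of 0.5, for assumed per-test rates of 10% to 30%. These rates and correlations, and the independence of use days, are assumptions. The conclusion that the count exceeds the per-test rate and rises with tests attended does not depend on their exact values, short of perfect correlation.

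This bears on a secondary, preliminary outcome and should be put right. It does not touch the primary feasibility outcome.

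**What to change.** 1. Show the baseline urine result as week 0 beside the weekly proportions for each target, with the number tested at each week.
2. For each target, report the within-person change from baseline as a simple paired estimate with a confidence interval. State which follow-up value is used and how many participants have no follow-up test. A GEE or mixed model is optional at this size.
3. Report the at-least-once count only among those off target at baseline (stimulant-positive; tenofovir-negative), with the number of tests attended, and label it descriptive.

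The interval should carry the message, not a test. In a simulation of an exact McNemar comparison with 40 independent pairs, the false-positive rate was about 3% with no change. Power was about 36% for a rise from 30% to 50%, and 69% for 30% to 60%. In a single-arm trial a paired change still does not attribute the change to the program.

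The cost is a little extra analysis, as the baseline results are already among the collected data. The Results section says the quantitative analysis had concluded as of June 2025, so anything added after that should be labelled post hoc.
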